### Recruitment process

Patient eligibility is confirmed with the treating clinician. The study is further explained to patients by a trained data manager and written consent is obtained. Patients are approached zero to six months prior to the end of treatment (preferably), or up to six months after the end of treatment. Once the study coordinating centre receives a patient randomisation request by fax or email from a participating site, the patient is randomised 1:1 to either usual care or SurvivorCare (100 patients are expected in each arm). The type of treatment and hospital site is entered in an Access database, where the allocation is balanced by site using a minimisation method. Figure 1 illustrates a schematic diagram of the study design.

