### Sample size requirements

The primary outcome for this longitudinal randomised controlled trial is psychological distress as assessed by the BSI-18 Global Severity Index, an 18-item scale with a possible range of 72. The BSI-18 will be completed once at baseline and twice post-intervention, but the main contrast of interest is the difference between arms at the first post-intervention follow-up.

In this case, we based our sample size calculations on 80% power, a two-sided *t*-test with an alpha-level of 0.05, a difference between groups of 3.6 points on the primary outcome (or 5% of the instrument range) [32] and a standard deviation of 8.6 [24] (a standardised difference of 0.42). Given these specifications, the required sample size is 180 patients (or 90 patients per arm). Assuming attrition of up to 10%, 200 patients will need to be recruited (or 100 patients per arm). Furthermore, assuming an 80% recruitment rate, approximately 250 patients will need to be approached to achieve a total sample of 200 patients. Patients will be recruited over 24 months.

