### Statistical analysis

Analyses will be by intention-to-treat and performed in SPSS Windows Version 21.0 (or higher) (Chicago, IL, USA). Prior to formal analyses, descriptive statistics and graphical displays will be used to identify missing and out-of-range values, assess the distributional characteristics of test scores and summarise study measure completion rates and missing data points. Responses to the BSI-18, DT, CaSUN, EORTC QLQ C-30 and CR-29 will be scored according to algorithms in the users’ manuals for these instruments.

Descriptive statistics will be used to summarise baseline demographic and clinical characteristics of patients randomised to the intervention and usual care. Recruitment bias and possible differential attrition will be assessed by comparing basic demographic and clinical characteristics of responders and non-responders, as well as drop-outs and continuing participants, using *t*-tests (or Mann–Whitney U) and chi-squared tests as appropriate.

Primary and secondary outcome analyses will be carried out by fitting a linear mixed model to each outcome separately using all available data. A cell means model will be used to estimate mean scores for each group by time combination. An unstructured covariance type will be used to model the covariance structure among repeated measures and all models will be estimated by maximum likelihood. Group comparisons at post-baseline time points will be performed using contrasts within the proposed models. After inspection of the data, the appropriateness of stated methods will be revised, if necessary. Because of the number of significance tests for secondary outcomes, Hochberg’s modified Bonferroni procedure will be used so that the overall type I error rate does not exceed 0.05 [33].

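### Allocation is minimised by hospital site, but the stated mixed model has no site term, so the test is mildly conservative if site is prognostic (minor)

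*Protocol article*

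**What the plan says.** On allocation, the Recruitment process section states: "The type of treatment and hospital site is entered in an Access database, where the allocation is balanced by site using a minimisation method". Two variables are entered, but balance is claimed for one of them, site. Design and setting gives 18 sites, and randomisation is 1:1.

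On analysis, the Statistical analysis section states: "Primary and secondary outcome analyses will be carried out by fitting a linear mixed model to each outcome separately using all available data". It goes on to fix the mean structure (one mean per group and time), the covariance (unstructured across a patient's repeated measures), the estimator (maximum likelihood) and the comparisons (group contrasts at the post-baseline times). Neither site nor treatment type is named as a fixed or random term. The section also allows the methods to be revised once the data have been looked at.

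On size, the Sample size requirements section uses "a two-sided *t*-test with an alpha-level of 0.05", that is, an unadjusted comparison, and names the between-arm difference at the first follow-up as the main contrast.

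**The concern.** Balancing allocation on a prognostic factor removes that factor's contribution to the chance difference between arms. A model that omits the factor still counts its variance as noise. The reported standard error is then larger than the true one, the confidence interval is too wide, and the test rejects less often than its nominal level.

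Site could plausibly matter here. Control patients receive each centre's own usual care, the intervention nurse may be a colorectal specialist or a general oncology nurse, and some sites have a single nurse for both arms. At stake is a little precision on the primary outcome, and on every secondary outcome analysed with the same model. There is also a question of timing: if adjustment for site is left to the revision step after data inspection, the choice could be made with outcomes in view.

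**Working it through.** **Inputs from the article (Sample size requirements).** Power 80%; two-sided alpha 0.05; difference 3.6 points; SD 8.6 (standardised difference 3.6/8.6 = 0.419, stated as 0.42); 90 per arm evaluable, 180 in total; attrition 10%.

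**Reproducing the plan's figure.** n per arm = 2 × (1.960 + 0.842)² × (8.6/3.6)² = 2 × 7.85 × 5.71 ≈ 89.6, so 90. The exact t calculation gives 91, or 90 with the rounded 0.42, so the stated figure stands. 180/0.90 = 200 recruited. Power at 90 per arm is 80.2% (normal approximation; 79.8% by exact t).

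**Input that the article does not give.** The share ρ of BSI-18 variance due to site. I take 0 to 20% as an assumed range, holding the total SD at 8.6.

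**Formulas, with perfect balance within site.**
- Model SE without site: 8.6 × √(2/90) = 1.282.
- True SE of the arm difference: 1.282 × √(1−ρ).
- Type I error of the unadjusted test: 2 × [1 − Φ(1.96/√(1−ρ))].
- Unadjusted power: Φ[(3.6 − 1.96 × 1.282)/true SE].
- Site-adjusted power: Φ[3.6/true SE − 1.96].

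Worked case, ρ = 0.10: true SE = 1.282 × 0.949 = 1.216. Type I error = 2 × [1 − Φ(2.066)] = 3.9%. Unadjusted power = Φ(1.087/1.216) = Φ(0.894) = 81.4%. Adjusted power = Φ(2.960 − 1.960) = Φ(1.000) = 84.1%.

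| Site share ρ (assumed) | SE too large by | Type I error, unadjusted | Power, unadjusted | Power, site-adjusted | Power forgone (points) |
|---|---|---|---|---|---|
| 0 | 0% | 5.0% | 80.2% | 80.2% | 0 |
| 0.02 | 1.0% | 4.8% | 80.4% | 81.0% | 0.6 |
| 0.05 | 2.6% | 4.4% | 80.8% | 82.2% | 1.4 |
| 0.10 | 5.4% | 3.9% | 81.4% | 84.1% | 2.7 |
| 0.20 | 11.8% | 2.8% | 82.9% | 88.1% | 5.2 |

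**Check by simulation.** The setting was 18 sites of unequal size, 180 patients, one time point, and minimisation by site that favours the lagging arm with probability 0.8 (assumed).
- *Unadjusted test* (20,000 replicates): type I error 5.0, 4.9, 4.4, 4.2 and 3.3% at the five values of ρ. This is slightly less conservative than the table at the larger values, because balance is not perfect. Power was 79.8 to 83.0% throughout.
- *Site as fixed effects* (20,000 replicates): power changed by −1.0, −0.4, +0.8, +2.1 and +4.5 points.
- *Site as a random intercept* (4,000 replicates): power changed by +0.2, +0.6, +1.1, +2.3 and +4.8 points, with no penalty at any value tried.

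With 200/18 ≈ 11 recruited patients per site, the random intercept is the more economical choice.

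**The case against.** Four points can be made for the plan.

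*The article is condensed, and a fuller plan may list covariates.* That is possible, and silence on a covariate is weaker than a stated error. But the section is not silent on the model. It fixes the mean structure, covariance, estimator and contrasts, and the model so described omits the factor on which the design balances.

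*The trial loses nothing that it planned.* This stands. The sample size was set for an unadjusted test, and unadjusted power stays at about 80% or above across the whole range. A reader might infer that the trial is underpowered or its type I error inflated. Neither follows: the loss is only relative to an adjusted analysis, and the error is in the conservative direction.

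*The size is unknown.* This also stands. No site effect is given. At a share of 0 to 2% the gain is about nil, and with fixed site effects slightly negative.

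*Stable site effects cancel in a change score.* The primary hypothesis speaks of benefit from baseline to Follow-up 1, which can be read that way. The sample size section, however, names the between-arm difference at the first follow-up, and the analysis uses contrasts at post-baseline times. Such a contrast does not remove site effects.

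A further tempting step is to treat site and treatment type together as balanced and to attribute conservatism to their combined share of variance. The article claims balance by site only. A factor left to chance acts as ordinary residual variance, and the test keeps its nominal level for that share. If, for illustration, site explained 2% and treatment type 8%, type I error would be about 4.8%, not the 3.9% of a balanced 10%.

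**Conclusion.** The point holds, as a minor one. The design balances by site and the stated model ignores site. If site is prognostic, the primary test is mildly conservative and its interval slightly wide. At an assumed site share of 5 to 10%, type I error is about 4.4 to 3.9% and the power forgone about 1.4 to 2.7 points; below 2% there is little to gain. There is no bias and no threat to the validity of the result.

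These sizes rest on the assumed site share, an SD of 8.6, 90 evaluable per arm, near-perfect balance within sites, and the follow-up contrast being primary. Confidence is high that design and model do not match, and moderate on how much it matters. Whether treatment type is a minimisation factor cannot be told from the article. That is a separate point of wording, outside the conservatism argument.

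**What to change.** In Statistical analysis, add a sentence stating that all primary and secondary models include hospital site as a random intercept, and settle this before any data are inspected. In the same sentence, treatment type can be added as a pre-specified fixed effect: it is already recorded at randomisation and plausibly predicts distress and quality of life. In Recruitment process, state whether treatment type is a minimisation factor or is only recorded.

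The cost is two sentences and a few degrees of freedom. No new data are needed and the sample size does not change.

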**Figure 1 F1:**
[figure not shown]
Schematic diagram of Survivor Care study design.

### Intervention group/SurvivorCare

The intervention consists of four main components: (1) information package; (2) nurse-led face-to-face end of treatment session; (3) SCP; and (4) telephone follow-up.

(1) Information package

The package includes a DVD (Just Take It Day to Day) [19], a booklet (*Life After Cancer*) [20], and a Question Prompt List (QPL). The QPL is a list of 70 questions covering common issues cancer survivors encounter in the first year following treatment. Ten main topics covering issues and concerns around coping, physical consequences of completing treatment, late and long-term effects of treatment, impact on family and friends, recurrence, follow-up planning, fertility, pregnancy and menopause, sexuality, dealing with practical matters, such as finances, returning to work and insurance, and need for further information and support, are listed to help the patient think about what they might like to ask their nurse or doctor. The patient is asked to view the material and complete the QPL prior to the nurse-led face-to-face session.

(2) Nurse-led face-to-face session

A nurse-led end of treatment session will take place in a standard timeframe after randomisation. Focus group results and a review of the literature [17] and expert input were used to design the end of treatment session, which addresses current concerns, seeks to attain a sense of closure on treatment and aims to prepare people for the survivorship phase and introduce telephone follow-up. The session takes place in a private hospital clinic room by a nurse trained to deliver the intervention. Session time is 60 to 90 minutes. Significant others are encouraged to also attend the end of treatment consultation to maximise the positive impact on patient outcomes [21,22]. Additional concerns not covered in the session are covered in subsequent telephone follow-up sessions. The session incorporates seven elements.

### Normalising treatment completion concerns

The vast majority of patients feel a degree of uncertainty for what lies ahead. Discussing treatment completion and the future will be addressed for all patients in the intervention arm.

### Tailored, evidence-based information and advice

At the beginning of the session, survivors score their current level of distress using the Distress Thermometer (DT) and indicate any queries or questions using the QPL. Level of distress noted on the DT and problem areas identified through the QPL will be used to guide a discussion of individual needs and prompt referral to other services. The patient will be asked to identify their top three concerns for focus during the session. Evidence-based self-management strategies will be provided to deal with side-effects. An intervention manual includes evidence-based guidance regarding all 69 questions from the QPL; together with additional information and resources (for example, information and support services for people with a stoma or managing continence issues). All information, processes and outcomes from the session are recorded in an End of Treatment Session Checklist.

### Referral to multi-disciplinary and community referrals

Survivors may experience a range of unmet supportive care needs. Research shows that nurse co-ordinated multi-disciplinary and community referrals result in better symptom control for cancer patients [23]. Nurses will offer (and organise where necessary) appropriate multidisciplinary and community referrals for unmet needs identified on the problem checklist from the DT or QPL.

### Recommendations regarding follow-up and discussion of the survivorship care plan

The SCP includes details of the cancer diagnosis, treatments, health promotional advice, supportive care and psychosocial elements, as well as recommendations for follow-up to detect cancer recurrence. The SCP will be reviewed and the importance of follow-up to screen for physical and supportive care issues will be emphasised. Patients will be given a SCP during the end of treatment session. Their general practitioner and oncology specialists will also be sent a copy.

### Liaison with the patient’s GP

Patients will be encouraged to discuss aspects of their survivorship care that might be best transitioned to their GP. Discussion will also cover aspects of care being managed by the patient’s GP and aspects of care for management by the specialist. This will be documented in the SCP. Patients will be advised that their GPs will also receive the SCP and recommendations regarding detection of cancer recurrence and screening for survivorship needs. The benefits of shared care with the GP will be emphasised. Thus, the transition from intensive hospital treatment to community-based GP maintenance, mediated through nurse-led phone follow-up will be encouraged. Discussion will also include appropriate time points for follow-up by medical specialists.

### Coaching

Health promotional strategies, such as stopping smoking, exercising and losing weight will be discussed where these are identified as issues for the survivor or the health professional. Intervention nurses will be trained to assess patients’ readiness to make behavioural change and will assist participants to establish behavioural change goals. Coaching and rehearsal of self-care for side-effects and stress-reduction strategies will be offered and reinforced during telephone follow-up sessions.

### Referral to peer support programs

All participants will be referred to peer support programs. Cancer Councils operate a free, one-to-one telephone-based peer support program called Cancer Connect. Volunteers are CRC survivors who have received rigorous training, including communication skills (asking open questions, empathy, active listening) and encouraging coping and adherence to self-care and health promotional advice. Patients will also be advised of other community-based resources, including cancer support groups and the Cancer Council Helpline.

### Nurse-led telephone follow-up

These sessions will take place one, three and seven weeks after the first intervention session. The purpose of the sessions are to: a) support the patient during the post treatment completion period to reduce feelings of isolation or abandonment from the hospital team; (b) revisit needs discussed during the end of treatment session and explore in detail and respond to any concerns not addressed at that session; (c) screen for psychosocial distress and additional unmet needs using the Distress Thermometer, issues highlighted in the QPL and the Survivor Care Plan; (d) encourage adherence to recommended self-care strategies and planned health behaviour change goals, and (e) emphasise the collaborative relationship between the patient’s GP and hospital team, highlighting that the patient’s GP has been provided with relevant information to enable effective shared care. Appointments will be made for the three calls, at the end of treatment session. The patient’s shared care team will be notified of any new concerns identified by the patient or nurse during telephone follow-up, as well as significantly high levels of psychosocial distress, and additional unmet needs. New patient concerns will be followed up by the intervention nurse at subsequent telephone follow-ups. Table 1 offers a summary of the elements covered by the intervention during the initial and follow-up sessions.

**Table 1 T1:** Features of the intervention covered during the post end of treatment sessions

**Elements of the SurvivorCare**	**Covered**	**Covered during**
**intervention**	**during initial**	**follow-up**
	**session**	**sessions**
Discussion of the survivorship care plan and introduction to follow-up	Yes	
Coaching	Yes	
Referral to peer support programs	Yes	
Normalising of common end of treatment concerns	Yes	
Discuss current concerns and advice	Yes	Yes
Referral to multi-disciplinary and community referrals	Yes	Yes
Screen for distress	Yes	Yes
Encourage adherence to self-care strategies	Yes	Yes
Promote shared care/GP involvement	Yes	Yes

### Usual care/control group

Participants allocated to usual care will receive care according to the treating centre/practitioner’s usual practice. Key elements of the intervention will not be provided in the control group (tailored, nurse-led, face-to-face and telephone sessions, question prompt list, self-care resources, SCP and GP correspondence). Participating health care services will be asked not to incorporate similar elements into usual care for the duration of the study. Participants allocated to the usual care group will be asked whether they have received any components of the SurvivorCare intervention, for example, information materials, SCP.

### Intervention staff training

Intervention nurses with experience looking after people with bowel cancer have been trained to provide the end of treatment and telephone follow-up sessions at each site. An expert in communication skills training and two experts in nurse-led clinics and self-care education conducted a full-day training program comprising: (a) an overview of the project, emphasising prevention of diffusion of the intervention at the site; (b) explanation of how to use the intervention manual; (c) training in eliciting and responding to emotional cues, including dealing with distress; (d) instruction on exploring concerns and providing evidence-based advice; (e) instruction in how to effectively facilitate referral to multidisciplinary team members; (f) instruction on how to coach patients to use evidence-based strategies; (g) role-play with simulated patients (actors) and activity sessions to practice the intervention, including self-appraisal and constructive feedback.

### Data manager training

Data managers (DMs) with experience in participant recruitment and coordinating research projects were trained to identify eligible patients, liaise with hospital staff and intervention nurses, approach patients, administer surveys, manage participant databases, and report data back to the project team. DMs were also trained on patient randomisation techniques.

### Study integrity and quality assurance

Efforts will be made to ensure that the intervention nurse will not be involved in follow-up of patients receiving usual care, to avoid contamination. At sites where only one nurse is available to administer both the intervention and usual care to patients, the intervention nurse will be given specific training to ensure that patients in the control group will not be given additional post-treatment care in addition to usual care.

A usual care checklist will be sent out with the first follow-up questionnaire to all patients in the usual care arm to determine whether patients have received elements of the intervention, such as the DVD, the booklet or SCP.

An intervention manual summarising details of the intervention was developed to train the nurses delivering the intervention. Intervention procedures will strictly be monitored for adherence to the manual. All intervention sessions will be audio-taped. The first 10 sessions will be reviewed to ensure adherence against a checklist derived from the manual. After this, a random sample of 15% of all sessions will continue to be reviewed. To ensure that competency is maintained, regular feedback sessions will be arranged.

Reasons for attrition will be recorded, and recruitment and drop-out bias assessed.

### Data collection procedure

Participants will be asked to complete a baseline questionnaire on the day of randomisation and two subsequent follow-up questionnaires at eight weeks (Follow-up 1) and six months (Follow-up 2) after the face-to-face session for the intervention group or after randomisation for the usual care group. Table 2 shows data to be collected.

**Table 2 T2:** Time points measuring patient reported outcomes for the SurvivorCare study

**Time point**	**Questionnaire**
Baseline: on the day of randomisation (zero to two weeks before a potential first intervention session)	Demographic variables, Medical records, BSI-18, DT, CaSUN, EORTC QLQ C-30 and CR-29.
Follow-up 1: eight weeks after randomisation date for usual care patient or after the first session date for intervention patients	BSI-18, DT, CaSUN, EORTC QLQ C-30 and CR-29 and Satisfaction Measure with usual care checklist
Follow-up 2: six months after randomisation date for usual care patient or the first session date for intervention patients	BSI-18, DT, CaSUN, EORTC QLQ C30 and CR-29

BSI-18, Brief Symptom Inventory; CaSUN, Cancer Survivors’ Unmet Needs Measure; DT, Distress Thermometer; EORTC QLQ C-30, European Organisation for Research and Treatment of Cancer core questionnaire; EORTC QLQ CR-29, the colorectal cancer module.

